#### Secondary Outcomes

Parameters necessary to estimate the time and budget required for the main study, which include the following:

Quantitative parameters, such as monthly recruitment rate, duration of enrollment and visits, choice of end points, and measurement.Qualitative parameters, such as information on patient reluctance to enroll, difficulty understanding the consent form, logistic issues at the site, interpersonal relationships among staff, and patient-reported QoL measured by the KOOS questionnaire (paper printed version) and the Lequesne Algofunctional Index (which also includes physical activity questions).

At the end of the pilot trial, the following criteria are used to determine whether to proceed with the future main RCT: there must be evidence of improvement in both the subjective outcome (VAS at rest) and at least one of the objective outcomes (ROM and ultrasound) at the final visit. On the contrary, due to the small sample size, a statistically significant correlation (using the Pearson coefficient) between objective and subjective parameters is not required.

#### Exploratory Outcomes

In addition to the primary and secondary outcomes, we identify exploratory outcomes that could be implemented in the main trial:

Actigraphy: This specific tool measures physical activity levels using a triaxial accelerometer that collects 24/7 data points during the patient’s daily activities. The investigator downloads and processes the data using specific software during routine visits at the center. The instrument is available in the market and has already been tested in OA clinical trials to objectively evaluate the composite measurement of pain and basic activities such as walking or performing daily tasks [31,32]. In this pilot study, an actigraph is worn around the knee to record data for 7 days.Rescue medication: Measuring the use of rescue medication during a clinical trial can provide information on the robustness of the analgesic efficacy of the tested product. Rescue medication may also be used as a primary end point according to the US Food and Drug Administration guidelines [33].

This study also provides preliminary data on the efficacy of the tested product.

### Framework of the Study

Before any study procedure, patients receive information about the nature, purpose, benefits, and risks of the trial. Participants are then asked to sign an informed consent form. After the screening assessment (from day –14 to day 0), patients undergo a BL visit (day 0) to assess the inclusion and exclusion criteria and check for routine orthopedic conditions (Figure 3). To confirm the diagnosis of knee OA, the investigator evaluates an x-ray test with anteroposterior and lateral views that are no earlier than 6 months old.

At BL (Table 1), the investigator also performs an ultrasound, ROM test, VAS, and the KOOS questionnaire. The actigraph must be placed above the affected knee 7 days before the visit and removed at BL. Safety is assessed by phone at week 4 ± 2 days, or an optional visit should be conducted to complete the questionnaires, scales, and scores.

The final visit is scheduled for week 8 ± 4 days to conduct an ultrasound, ROM assessment, VAS, and the KOOS questionnaire. Patients wearing the actigraph will also be asked to return to the site 7 days before the visit to place the device above the affected knee; it will be removed during the final visit.

**Figure 3 figure3:**
[figure not shown]
Flow diagram (CONSORT [Consolidated Standards of Reporting Trials]) of the pilot study.

**Table 1 table1:** Schedule of observation points and assessments.

Assessments	Visit 1	Visit 2	Visit 3
Days	–14 to 0	28 (±2)	56 (±4)
Weeks	–2 to 0	4	8
Informed consent	✓		
Inclusion criteria	✓		
Exclusion criteria	✓	✓	✓
Demographics and medical history	✓		
Physical examination and vital signs	✓		
Orthopedic assessment	✓		✓
Concomitant treatments	✓	✓	✓
Actigraphy—sensor delivery (1 week before the visit; optional)	✓		✓
Actigraphy—sensor return (optional)	✓		✓
KOOS^a^	✓	✓^b^	✓
VAS^c^	✓	✓^b^	✓
ROM^d^ by a goniometer	✓	✓^b^	✓
Ultrasonography	✓		✓
IP^e^ delivery	✓		
IP return			✓
Rescue medication delivery	✓		
Rescue medication return			✓
Rescue medication accountability card delivery	✓		
Rescue medication accountability card return			✓
Adverse events	✓	✓^f^	✓

^a^KOOS: Knee Injury and Osteoarthritis Outcome Score.

^b^Tests and examinations not mandatory if the visit is performed via telephone call.

^c^VAS: visual analog scale.

^d^ROM: range of motion.

^e^IP: investigational product.

^f^Safety (adverse event or serious adverse event checking) is mandatory in any case.

### Sample Size

For feasibility and pilot trials, it is important to justify the sample size; however, a formal calculation may not always be necessary [34] and is often not reported. In fact, a pilot study is not a hypothesis testing study, and often its main purpose is to test the feasibility of the proposed approach. This involves testing quantitative parameters, such as outcomes and resources, as well as qualitative factors, such as QoL and logistical issues at the site.

Although some papers suggest a sample size of 12-20 participants for pilot studies, it is generally reported that 10%-20% of the main sample size is a reasonable number for conducting such trials [35]. Given that the sample size of our main RCT will be 80 patients and the exploratory nature of this pilot study, investigators have agreed to enroll only 8 participants.

### Statistical Analysis

Quantitative variables, such as demographics, are described using mean and SD if normally distributed and median and IQR if nonnormally distributed. Comparative analysis is performed using either the Student *t* test (2-tailed) or the Mann-Whitney *U* test, depending on the distribution of the variables. Factorial variance analysis can be used to evaluate interactions between quantitative variables and linear progression models to identify possible confounding bias with independent variables. Categorical variables are described using frequencies and percentages, and comparative analyses using the χ^2^ test. The Spearman rank correlation, a nonparametric test, measures the degree of association between 2 variables. The Spearman rank correlation test is appropriate for analyzing correlations when variables are measured on at least an ordinal scale, as is the case in this study. This test does not make any assumptions about the distribution of the data. When analyzing the enrolled population, we use the Spearman rank correlation test to identify any strong positive correlations (at least 0.7) between the reduction in VAS (at rest) and ultrasound parameters, as well as between the reduction in VAS (at rest) and ROM improvement.

We evaluate the quality and completeness of the collected data before conducting any analysis. If a participant is missing information for 1 or more variables, even after the queries are resolved, the missing data are not replaced. Additionally, if a participant has violated the inclusion and exclusion criteria, the corresponding data are excluded from the analysis.

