### Study Design

This is an open-label, noncontrolled, single-center pilot feasibility study.

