### Outcomes

#### Primary Outcomes

ROM: The improvement in active and passive knee flexion and extension, measured in degrees using a goniometer and assessed by the investigator, between the BL visit and the final visit.Ultrasound: A qualified physician records improvements in ultrasound parameters including synovial fluid, articular cartilage damage, medial meniscus protrusion, lateral meniscus protrusion, medial osteophytes, lateral osteophytes, enthesopathies, and effusions.VAS: The improvements in VAS (at rest) scores between the BL and final visit are measured in millimeters. A paper printed scale of 100 mm was used to measure pain intensity. Patients must draw a vertical line at the point considered to be the level of pain at a specific moment, that is, resting, moving, or pressing.Safety: Investigators must collect and evaluate all AEs and SAEs according to the current local legislation. AEs and SAEs must be summarized based on the number of affected patients. This includes related AEs, including those that are possibly related to or not evaluable. The incidence, type, and severity of AEs or SAEs are presented in frequency tables using MedDRA (Medical Dictionary for Regulatory Activities) terms. Frequency is compared using the χ^2^ test

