### Limitation of the Study

The main limitation of this study is the absence of a control group. In fact, to reduce costs and simplify the protocol, the placebo group was not included.

A second limitation is that the IP used does not contain HA alone, but a combination of HA and a very low amount of boswellic acid (10% AKBA). With such a low dose of AKBA, only 1 study [45] showed positive results for the treatment of OA. This study used a product that contains 14.4 mg of AKBA combined with a high dose of methylsulfonylmethane, a well-known SYSADOA. Therefore, it can be assumed that in the pilot study, the effect of HA should be more prevalent than that of AKBA.

Finally, the KOOS questionnaire is used in this pilot study, although the WOMAC is the most widely used test for evaluating hip and knee OA. The KOOS evaluates both the short- and long-term consequences of knee injuries. The KOOS is selected for this study as it is a free and open-access alternative to the expensive WOMAC index. The KOOS is an extension of the WOMAC.

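### The named tests do not fit a one-group before-after design: Mann-Whitney U and chi-square assume independent samples, and no paired method is named

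*Protocol article*

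**What the plan says.** All references are to the protocol article.

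- Study Design: "This is an open-label, noncontrolled, single-center pilot feasibility study". Limitation of the Study confirms it: "The main limitation of this study is the absence of a control group".
- Sample Size: "investigators have agreed to enroll only 8 participants".
- Primary Outcomes, VAS: "The improvements in VAS (at rest) scores between the BL and final visit are measured in millimeters".
- Primary Outcomes, ROM: "measured in degrees using a goniometer and assessed by the investigator, between the BL visit and the final visit".
- Primary Outcomes also lists improvements in ultrasound parameters. Table 1 schedules ultrasonography at Visits 1 and 3.
- Inclusion Criteria: in bilateral disease one knee is chosen at baseline and followed for the whole study.
- Statistical Analysis: "Comparative analysis is performed using either the Student *t* test (2-tailed) or the Mann-Whitney *U* test", depending on how the variable is distributed. Categorical variables are compared by chi-square.

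No paired t test, Wilcoxon signed-rank test, McNemar test or repeated-measures method is named in any section.

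**The concern.** With one group measured twice, a test of efficacy has to compare each patient with himself or herself. Mann-Whitney U and chi-square treat the two sets of values as coming from different people. The t test could be either form. However, the usual nonparametric partner of a paired t test is the signed-rank test, and Mann-Whitney is the partner of the two-sample test.

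This is not a detail left to an analysis plan. The article names specific tests, and at least two of them do not fit the design it describes.

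At stake is the quality of the preliminary efficacy data, which Objectives lists among the aims. Analysing 8 pairs as 16 unrelated values discards the within-patient correlation, which is the main source of precision in a before-after study.

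**Working it through.** **The plan's own figure.** Sample Size reasons that "it is generally reported that 10%-20% of the main sample size is a reasonable number for conducting such trials" and that "the sample size of our main RCT will be 80 patients". 10% of 80 = 8, so the stated size reproduces. No alpha, power, SD or effect size is given, so there is no power figure to reproduce.

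**Inputs.** From the article: n = 8 pairs, two-tailed testing. Assumed, because the article does not give them: a 5% level, equal SD (σ) at both visits, bivariate normal data, a true change of 1σ, and baseline-final correlation ρ of 0, 0.3, 0.5 and 0.7.

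**Standard error of the mean change.**
- Unpaired: σ√(2/8) = 0.50σ, whatever ρ is.
- Paired: σ√(2(1−ρ)/8), which is 0.50σ, 0.42σ, 0.35σ and 0.27σ at ρ = 0, 0.3, 0.5 and 0.7.
- Ratio unpaired/paired: 1/√(1−ρ) = 1.00, 1.20, 1.41 and 1.83.

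**Interval width.** The unpaired test has 14 degrees of freedom (critical value 2.145) and the paired test 7 (2.365). The width ratio is therefore (2.145/2.365)/√(1−ρ) = 0.907/√(1−ρ), which is 0.91, 1.08, 1.28 and 1.66. The ratio of mean simulated widths is slightly larger, because the sample SD of 8 differences runs a little low. The two intervals are equally wide at ρ = 1 − 0.907² ≈ 0.18.

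**Power of the paired t test.** The noncentrality is √8/√(2(1−ρ)) = 2.00, 2.39, 2.83 and 3.65 on 7 degrees of freedom. This gives 41%, 54%, 68% and 88%.

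**Simulation** (200,000 datasets per setting):

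| ρ | Unpaired t, type I error | Unpaired t, power | Paired t, power | Ratio of mean 95% CI widths |
|---|---|---|---|---|
| 0 | 5.0% | 46% | 41% | 0.92 |
| 0.3 | 2.4% | 46% | 54% | 1.10 |
| 0.5 | 1.1% | 46% | 68% | 1.30 |
| 0.7 | 0.3% | 46% | 88% | 1.67 |

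The paired t test stays at about 5% throughout. The nonparametric branch behaves the same way: in a separate run of 20,000 datasets at ρ = 0.5, Mann-Whitney had 43% power and the exact signed-rank test 61%.

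**Categorical branch.** Suppose a finding is present in 6/8 patients and then in 2/8, with four patients changing, all one way. Chi-square without correction is 4.0, p = 0.046; exact McNemar gives 2 × 0.5⁴ = 0.125. Pairing does not explain this gap. McNemar without the exact calculation is (4−0)²/4 = 4.0, again p = 0.046, and Fisher's exact test, which ignores pairing, gives 0.132. The difference comes from using a large-sample approximation on 8 patients. The example supports an exact method. The objection to chi-square on pairing grounds is simply that its independence assumption fails.

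**The case against.** **The t test may be paired.** Statistical Analysis does not tie its tests to the baseline-final contrast, and the paragraph opens with demographics as its example. A reader might infer that the plan definitely uses an unpaired t test. The text does not establish that. What stands is that Mann-Whitney and chi-square are independent-sample tests under any reading, and that no paired alternative is offered.

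**The go decision.** A reader might infer that the decision to start the main trial will be read from the wrong test. Secondary Outcomes and the Discussion ask for evidence of improvement in VAS and in at least one objective measure, but name no test, p value or level. Objectives and Sample Size both say that significance testing is not the purpose. The documents therefore do not support a direct effect on that decision.

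**Direction and size.** For VAS and ROM the error is conservative, so it would not produce false claims of improvement. The loss is small at ρ = 0.3. At ρ = 0 the unpaired t test holds its level and is slightly more powerful. This stands, and is why the range is shown.

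**Part of the plan already uses change scores.** The Spearman analysis correlates the reduction in VAS with the improvement in ROM, patient by patient. That analysis is unaffected.

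**Separate matters.** Choosing a test by the observed distribution of 8 values is weak practice, and the factorial and confounder models are ambitious for 8 patients. The models are optional, and neither issue is needed for this point.

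**Conclusion.** The point holds in limited form and should be fixed. The tests named do not match a single-arm before-after design: this is certain for Mann-Whitney U and for chi-square applied to before-after findings, and probable for the t test.

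If the tests are applied as written to VAS and ROM, reported p values will be too large on average and the implied intervals too wide whenever the visits are positively correlated by more than a little. At ρ = 0.5, 68% power falls to 46% and the interval is about 1.3 times as wide. These sizes rest on the assumed correlations, the 1 SD change and the 5% level, none of which the article states. The article plans no confidence intervals, so the width figures describe the interval implied by an unpaired analysis.

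The harm is to the reported p values and to the precision of the preliminary efficacy estimates.

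**What to change.** In Statistical Analysis, replace the comparative tests for before-after outcomes with:

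- VAS and ROM: paired t test, reporting the mean within-patient change with its 95% CI; Wilcoxon signed-rank as the nonparametric alternative.
- Ordinal ultrasound scores: Wilcoxon signed-rank.
- Binary ultrasound findings: exact McNemar.

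Primary Outcomes does not give the scale of each ultrasound parameter, so each should be assigned to one of these methods by its type.

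The cost is small. The wording change is one paragraph and no new data are needed. Results says that treatment ended in May 2018 and that analysis was planned to finish that year; if it was run as written, it must be rerun on the same data. Exact McNemar is also demanding at this size: two-sided p falls below 0.05 only if at least 6 of the 8 patients change, all in one direction (5 changes give 2 × 0.5⁵ = 0.0625; 6 give 2 × 0.5⁶ = 0.031). Binary findings are therefore better presented mainly as counts of patients who changed.

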### Intervention

All patients will receive Syalox 300 Plus (River Pharma), a food supplement containing HMWHA. Although this product has been available in European countries for several years and has been used in the clinical practice by hundreds of orthopedists, only a few clinical trials [18] have been conducted to test whether this type of product with oral HA could complement the treatment of patients affected by OA. In this study, the investigational product (IP) is administered as 1 tablet daily for 8 weeks, preferably before or during meals, with plenty of water. Following local legislation for food supplements, the product used is the same as that available in the market and must be administered as reported in the instruction for use. No changes in the dosage are planned during the study period. However, the investigator may decide to discontinue IP administration in case of adverse events (AEs) and serious AEs (SAEs) or to use other therapies at any time if he or she deems it necessary for the patient’s health. The reason for discontinuing the administration must be documented in both the source documents and CRF. At BL, each patient is given an IP package for the entire duration of the study (60 tablets). Patients are instructed to return all IP packages to the investigator at the end of the study to ensure product accountability. The IP contains 2 ingredients: HMWHA and dry extract of Boswellia.

A medical literature analysis has shown that HMWHA has been effective in relieving knee pain in various clinical trials without side effects [12,13]. The amount of HMWHA in the IP used in this study, which is greater than 2.8 million Da, is comparable to or slightly higher than that of supplements already available on the market for viscosupplementation in OA [13] and used in clinical trials [19-21].

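### In this single-arm study of 8 patients, the optional linear models cannot show whether the before-after change is confounded, and factorial ANOVA is misapplied to quantitative variables (minor)

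*Protocol article*

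**What the plan says.** The Statistical Analysis section of the protocol article allows two kinds of model in one sentence: "Factorial variance analysis can be used to evaluate interactions between quantitative variables and linear progression models to identify possible confounding bias with independent variables". Factorial ANOVA is assigned to interactions. The linear models (printed as progression, presumably regression) are assigned to confounding. The sentence names no outcome, exposure or covariate for either.

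Other sections fix the design in which these models would run:

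- Study Design: "This is an open-label, noncontrolled, single-center pilot feasibility study".
- Intervention: "All patients will receive Syalox 300 Plus (River Pharma), a food supplement containing HMWHA", and "No changes in the dosage are planned during the study period".
- Sample Size: "investigators have agreed to enroll only 8 participants".
- Limitation of the Study: "The main limitation of this study is the absence of a control group".

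The Objectives and Statistical Analysis sections also plan to relate VAS reduction to ROM improvement and to ultrasound parameters, by Spearman correlation. The rule for going on to the main trial (Secondary Outcomes, repeated in the Discussion) asks for improvement in VAS at rest and in at least one objective outcome. No covariate model appears in it.

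**The concern.** A covariate confounds a treatment effect only if it is associated with treatment. Here treatment is the same for everyone, so no covariate can be associated with it and no treatment term can enter a model beside the intercept. A regression of change on, say, age tests whether age predicts change. It does not test whether the average change is due to the product.

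Bias from natural course, regression to the mean or expectation sits in the average change itself, and a slope test does not see it. A significant slope could therefore be reported as confounding found, and non-significant slopes as confounding excluded. Neither statement would be supported. The second would give an uncontrolled change more credit than it has earned.

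The ANOVA half of the sentence has its own fault. Factorial ANOVA crosses categorical factors, so it does not evaluate interactions between quantitative variables unless these are first cut into groups.

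**Working it through.** **Inputs from the article.** n = 8; one arm; same product and dose for all; main trial of 80. The article gives no alpha, SD, covariates or test-retest correlation for these models, so a two-sided alpha of 0.05 and the values marked as assumed below are illustrative.

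**The plan's own figure.** The Sample Size section says "it is generally reported that 10%-20% of the main sample size is a reasonable number for conducting such trials" and "Given that the sample size of our main RCT will be 80 patients". 0.10 × 80 = 8, which reproduces the stated n.

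**1. Identification.** Write the model as change = intercept + treatment + covariate. With treatment equal to 1 in all 8 patients, the design matrix has 3 columns but rank 2, and the SD of treatment is 0. The treatment effect cannot be separated from the intercept at any sample size.

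**2. Is the slope test blind to the bias?** Take two situations with an assumed SD of change of 20 mm: (A) treatment effect 0 and nonspecific change −15 mm; (B) treatment effect −15 mm and no nonspecific change. In 100,000 simulated trials of 8 patients each:

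| | A | B |
|---|---|---|
| Mean change (mm) | −15.0 | −15.0 |
| P(slope significant), covariate unrelated to change | 0.05 | 0.05 |
| P(slope significant), covariate correlated 0.7 with change | 0.545 | 0.545 |

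The results are identical whether the change is all treatment or all bias.

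**3. Precision at n = 8.** With one predictor there are 6 residual df and t(0.975; 6) = 2.447, so significance needs |r| ≥ 2.447 / √(2.447² + 6) = 0.707. Simulated power is 0.11, 0.25, 0.55 and 0.76 for true correlations of 0.3, 0.5, 0.7 and 0.8. About 0.82 is needed for 80% power.

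**4. The association of VAS with ROM or ultrasound.** A third variable can confound this, and regression could in principle address it. Adjusting for one covariate leaves 8 − 3 = 5 residual df. Then t(0.975; 5) = 2.571, and the partial correlation must reach 2.571 / √(2.571² + 5) = 0.75. With an assumed rule that a 10% change in the estimate marks a confounder, a true non-confounder is marked in about 40% of samples. A real moderate confounder (assumed: correlation 0.5 with the predictor, coefficient 0.5 on the outcome) is marked in about 69%. Confounding is defined here but hardly assessable.

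**5. Factorial ANOVA.** A 2×2 split gives 8 / 4 = 2 patients per cell and 8 − 4 = 4 residual df; a 2×2×2 split leaves 0. The interaction contrast has variance 4σ²/2 = 2σ². Power from the noncentral F(1, 4) is 0.059, 0.086 and 0.195 for interactions of 0.5, 1 and 2 SD.

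**6. How often would something be flagged?** Assume age, sex, BMI and baseline value as covariates, none related to true change, and test-retest correlation r. The share of trials with at least one p < 0.05 is:

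| r | 0.3 | 0.5 | 0.7 | 0.8 |
|---|---|---|---|---|
| One covariate at a time | 45% | 36% | 29% | 24% |
| Joint model (3 residual df) | 23% | 18% | 16% | 14% |
| Baseline value alone | 36% | 25% | 17% | 12% |

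Adding a wholly spurious 1-SD shift at r = 0.7 leaves the rates the same within simulation error (30% against 29%; joint 17% against 16%).

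Two things inflate these rates. One is multiplicity: four unrelated covariates alone give roughly 1 − 0.95⁴ = 18.5% (17–19% in simulation; about 12% jointly). The other is baseline value, which is built into change: with equal variances its correlation with change is −√((1 − r)/2), which is −0.5 at r = 0.5.

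**The case against.** The strongest reply is that little depends on the sentence. The models are optional, the rule for proceeding does not use them, and nothing in the article says that non-significant slopes would be reported as an absence of confounding. The article already names the missing control group as its main limitation. It also calls the efficacy data preliminary and says that a pilot is not a hypothesis test. All of this stands and limits the consequence.

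Three further objections are also right:

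- A reader might infer that the plan uses factorial ANOVA to look for confounding. It does not; the sentence gives ANOVA to interactions only.
- A reader might infer that confounding cannot be addressed anywhere in this study. That is too broad. For VAS against ROM or ultrasound the obstacle is precision, not identification. Rescue paracetamol is recorded and can vary between patients, so it too is not structurally beyond a model. In a simulation where rescue use caused the whole change (assumed linear effect, about 15 tablets on average, no confounding by indication), the crude mean change was −15.0 and the rescue-adjusted intercept 0.06, though with an SD of 7.0.
- The flag rates should not be set against 5%, which is a per-test level. Much of the excess is multiplicity, and part comes from including baseline value, a covariate that the plan does not name.

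None of this gives the linear models the ability to do the stated job for the before-after change, and none of it repairs ANOVA on quantitative variables.

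**Conclusion.** The point holds and is minor. For the before-after change, the linear models can show only whether a covariate predicts change. They cannot detect or rule out bias from natural course, regression to the mean or expectation. This follows from the single-arm design and needs no assumed figure. For the association of VAS with ROM or ultrasound, n = 8 is too small for a useful answer. The ANOVA wording is a separate fault.

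The any-flag rates of about 14–45% are illustrative. They rest on assumed covariates and test-retest correlations of 0.3 to 0.8, and they are partly multiplicity.

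A reader might go further and infer that the decision to start the 80-patient trial would rest on these models. The article does not support that: the decision uses the observed improvements alone. What is at stake is a misleading statement, beside the preliminary efficacy data, that confounding was or was not found.

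**What to change.** Replace the sentence in Statistical Analysis with wording to this effect:

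> Because all patients receive the product, confounding of the before-after change cannot be tested or excluded in this single-arm study. Each patient's baseline and final VAS, ROM and ultrasound values will be presented with age, sex and rescue tablets used, descriptively. Any regression, including of the association between VAS and ROM or ultrasound, is descriptive exploration, without p values and without a conclusion on the presence or absence of confounding.

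Drop the factorial ANOVA. If a regression is kept, name its outcome and covariates.

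The cost is a short change of wording, with no new data, patients or procedures. The only loss is an optional exploratory test that 8 patients cannot support.

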### Objectives

The primary objective of this pilot study is to test the same outcomes that will be implemented in the future RCT. This next trial will have a calculated sample size of at least 80 patients and a study duration of 4 months. Therefore, the feasibility of using ultrasound and range of motion (ROM) to objectively measure the potential improvement in the tested joint mobility during the trial is evaluated. Additionally, we investigate whether there is a correlation between ROM or ultrasound improvement and subjective VAS scores.

This pilot study, even if it is a small-scale investigation, should also confirm the safety data belonging to the large use of oral HA in clinical practice.

Another objective is to collect data to assess the feasibility of the future main RCT in advance, estimating the time and budget required. The collected data can be both quantitative and qualitative.

Finally, this study should provide preliminary data on the efficacy of the tested product. However, these data will not be exhaustive, as the focus of the pilot study is on the reliability of the outcome and feasibility of measurement, rather than statistical significance [29].

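### The correlation between VAS and the objective measures is specified inconsistently (Spearman or Pearson, change or unspecified) and flagged by a 0.7 cut-off that is weak with 8 patients and about 12 pairs

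*Protocol article*

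**What the plan says.** **Coefficient and cut-off.** Statistical Analysis (Protocol article, Methods) chooses the Spearman rank correlation because the variables are at least ordinal and no distribution need be assumed. It is used "to identify any strong positive correlations (at least 0.7) between the reduction in VAS (at rest) and ultrasound parameters", and likewise between VAS reduction and ROM improvement. Secondary Outcomes, when setting the conditions for the main trial, says that "a statistically significant correlation (using the Pearson coefficient) between objective and subjective parameters is not required".

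**Variables.** Objectives asks "whether there is a correlation between ROM or ultrasound improvement and subjective VAS scores". Primary Outcomes defines ROM and VAS as improvements from baseline to the final visit and speaks of improvements in the ultrasound parameters, which are "synovial fluid, articular cartilage damage, medial meniscus protrusion, lateral meniscus protrusion, medial osteophytes, lateral osteophytes, enthesopathies, and effusions". ROM covers active and passive flexion and extension.

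**Size and role.** Sample Size states that "investigators have agreed to enroll only 8 participants". The rule for proceeding (Secondary Outcomes, repeated in the Discussion) requires improvement in VAS at rest and in at least one objective outcome. It contains no correlation threshold.

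**The concern.** There are three faults in one analysis.

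- **Two coefficients are named for the same relation.** In 8 patients with ordinal findings, Spearman and Pearson can differ materially.
- **The variables are not fixed consistently.** Statistical Analysis pairs a VAS reduction with ultrasound parameters, without saying level or change, although ROM in the same sentence is an improvement. Objectives pairs ultrasound improvement with VAS scores, without saying change. The sign matters because only positive values count. If, for example, effusion were coded as final minus baseline, a real benefit would correlate negatively with VAS reduction and could not be flagged.
- **Any pair whose point estimate reaches 0.7 is called strong.** The number of pairs is not limited, and the label takes no account of imprecision.

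At stake is what the pilot reports on its primary objective. The Discussion goes further and suggests that correlated improvements could serve as an additional measurement tool in daily practice. A correlation called strong by chance would feed that claim.

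**Working it through.** **Inputs.** n = 8 (Sample Size). The protocol's own figure reproduces: 10% × 80 = 8. The cut-off is Spearman r_s ≥ 0.7, positive direction only (Statistical Analysis). There are 8 listed ultrasound parameters (Primary Outcomes). ROM gives 2 × 2 = 4 measures if active and passive flexion and extension are kept separate; this is inferred, since the document does not count them. Pairs: 8 + 4 = 12. The protocol gives no alpha, power or derivation for 0.7, so there is no figure of its own to reproduce.

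**1. False flag for one pair.** Enumerating all 8! = 40,320 rankings without ties and with no association: P(r_s ≥ 0.7) = 1,161/40,320 = 0.0288, or 2.9%. The smallest attainable value at or above 0.7 is 0.714.

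**2. At least one false flag among 12 pairs.** If independent: 1 − (1 − 0.0288)^12 = 0.296. All pairs share the same VAS variable and the objective measures will be related to one another, so this was also simulated:

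| Correlation among objective measures | P(at least one r_s ≥ 0.7) |
|---|---|
| 0 | 30% |
| 0.3 | 24% |
| 0.5 | 21% |
| 0.8 | 13% |

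For the 8 ultrasound pairs alone, if independent: 1 − (1 − 0.0288)^8 = 0.208.

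**3. Chance of flagging a real correlation in one pair** (bivariate normal, n = 8, simulated):

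| True correlation | P(r_s ≥ 0.7) |
|---|---|
| 0.5 | 22% |
| 0.7 | 46% |
| 0.8 | 64% |

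**4. Precision of an observed 0.7.** Fisher z: atanh(0.7) = 0.867; SE = 1/√(8 − 3) = 0.447; 0.867 ± 1.96 × 0.447 = −0.009 to 1.744. Back-transformed, the 95% interval is −0.01 to 0.94. With the Bonett-Wright standard error, √((1 + 0.7²/2)/5), it is −0.11 to 0.95.

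**5. Sensitivity to the assumptions.** Missing values are not replaced, so n per pair can fall below 8. The per-pair false-flag rate is 4.4% at n = 7 and 6.8% at n = 6. Ties also matter. If an ultrasound finding is binary and only 1 of 8 patients changes, the largest possible r_s is 0.58 and the flag cannot be reached. If 2, 3 or 4 change, the per-pair rate is 3.6%, 3.6% or 2.9%.

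**The case against.** The strongest reply is that this is a declared pilot. Objectives puts reliability and feasibility ahead of statistical significance, Sample Size says a pilot does not test hypotheses, and Secondary Outcomes and the Discussion waive significance of the correlation as a condition for the main trial. This stands. It would be unfair to fault 0.7 for lying below the two-sided 5% critical value (0.738 at n = 8), because the protocol claims no such test. But the waiver concerns the condition for proceeding. It does not cover calling a correlation strong when its interval reaches zero.

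It can also be said that the meaning is clear from context. Objectives and Primary Outcomes speak of ultrasound improvement, and the Discussion of correlating objective and subjective improvements. A reader might infer from Statistical Analysis that ultrasound levels are to be correlated. The text does not say so; it is silent there, and elsewhere it points to change. The fault is ambiguous wording with no stated sign convention.

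The Pearson mention is a single parenthesis, while the analysis section gives reasons for Spearman. That limits the consequence if the analysis section is followed, but the two statements still conflict.

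Finally, interval estimates and multiplicity handling may be in a full protocol or analysis plan that is not shown. Their absence is not the point here. The point is the cut-off that the article does fix.

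**Conclusion.** The point holds as a conflict in the named coefficient, loosely defined variables, and a weak point-estimate label within the primary objective. Assuming 8 complete patients, untied ranks and 12 pairs (4 of them inferred), the chance of at least one false strong correlation is about 13% to 30%. A true 0.7 is flagged about 46% of the time, and an observed 0.7 is compatible with anything from no association to a very strong one.

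Three stronger readings are not supported:

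- **That the cut-off cannot tell signal from noise.** For one pair it passes 2.9% of the time with no association and 46% at a true 0.7. The weakness comes from the number of pairs and the imprecision.
- **That a chance finding is likely.** Even the upper figure, which needs independent measures, is about 30%.
- **That the decision to start the main trial is at risk.** The rule for proceeding contains no correlation threshold.

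The risk is a misleading statement in the report.

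**What to change.** 1. Name Spearman in Secondary Outcomes as well as in Statistical Analysis, and delete the reference to Pearson.
2. In Objectives and Statistical Analysis, define both variables as baseline-to-final change, signed so that a positive value means improvement for VAS, each ROM measure and each ultrasound parameter.
3. Drop the 0.7 cut-off. Report each estimate with its 95% confidence interval and the number of patients behind it, and present all pairs as descriptive.
4. Optional: name one main ROM pair and one main ultrasound pair. A pilot that is meant to learn which measures are usable has reason to look at all of them, so this is a preference.

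Recruitment and treatment ended in May 2018 and analysis was planned for completion that year, so the change applies mainly to the report. Any choice made after the data were seen should be stated there.

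The cost is wording only: no patients, visits or measurements are affected. The downside is that the results will be shown as very imprecise.
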